### Outcome measurements

The primary efficacy variables are mitral inflow velocities (E and A waves), deceleration time of the E wave (DT), isovolumetric relaxation time (IVRT), mitral annular velocities (early diastolic velocity of mitral annulus (Ea) and late diastolic velocity of mitral annulus (Aa) waves), left atrial (LA) volume, and LA strain (global systolic and diastolic LA strain), which will be measured via echocardiographic evaluation after 12 months of treatment. Mitral E/A and E/Ea ratios will be calculated. Parameters from Doppler analysis, M-mode echocardiography, and 2D-transthoracic echocardiography will be used. All echocardiographic images will be interpreted by an observer who is blinded to clinical data.

Secondary outcomes include occurrence of clinical events. Symptom severity (NYHA classification) and hospitalization will be evaluated at baseline and at maintenance follow-up visits. Vital signs, including heart rate and blood pressure, will be measured at every visit. Any complications, discontinuations, and deaths occurring during the study period will be noted. Each patient’s medical history and the results of a clinical examination will be recorded at baseline by the attending physician.

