### Sample size

Calculation of sample size was done based on the primary outcomes and the primary analysis for the intention-to-treat population. The sample size was calculated using the study’s primary objective, to detect a difference in E/E’ of 5.0 between nebivolol and carvedilol treatment with a power of 90 %. On the basis of previous reports, we assume the standard deviation of E/E’ to be approximately 5.0 in both treatment groups [11, 12]. We adjusted the sample size for an estimated follow-up loss rate of 30 %, a two-sided level of significance *a* = 5 % and a power of 1 − β = 90 %. Thirty-one patients in each group are required to detect statistical differences with a two-sided Student’s *t* test given these parameters. Therefore, a total of 62 patients will be included in the analysis. The statistical analyses will be performed on the full dataset, which will include data from all randomized patients receiving at least one dose of study medication. Patients who are judged to be ineligible after study registration will be excluded from the analysis. Given the sample size, this study is likely to be underpowered in terms of assessing secondary outcomes.

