### Statistical analyses

The intent-to-treat (ITT) analysis set will be used for efficacy analyses. All patients who have begun treatment will be included irrespective of their protocol adherence and continued participation in the study. Patients will be analyzed according to their randomized study medication irrespective of whether a SAE occurred before or following discontinuation of study medication. For baseline characteristics, continuous variables will be assessed using the Student’s *t* test and discrete variables will be compared using the chi-square test. The primary outcome will be compared using two-sample *t* tests. The two-sided null hypothesis for the primary outcome measure states that nebivolol and carvedilol lead to the same change in ventricular diastolic function during the 12 months after diagnosis. This null hypothesis will be tested by regression analysis adjusted for baseline values. Assessments for other echocardiographic indices will be compared between treatment groups after 12 months of follow-up using two-sample *t* tests. Analyses of changes will be performed using data from all patients for whom baseline and 12-month follow-up data are available. Event-free cumulative survival rates will be plotted using the Kaplan-Meier method and comparisons will be made between patients given nebivolol and carvedilol using the log-rank test. A Cox proportional hazards model, with the use of forward selection based on the likelihood ratio test, will be implemented for multivariate analysis to determine which prognostic factors identified in the univariate analysis, including mitral inflow velocities, DT, IVRT, mitral annular velocities, LA volume, and LA strain were significantly related to clinical events in the follow-up period.

A safety analysis dataset will be used to assess safety and tolerability variables. All patients who received at least one dose of nebivolol or carvedilol, and for whom post-dose data are available, will be included in the safety population. Patients will be censored 7 days after their last dose of study medication. A value of *p* < 0.05 will be considered statistically significant.

Potential attrition bias will be mitigated by conducting dropout analysis and intention-to-treat analysis. Given that dropouts are expected, multiple imputation, based on regression methods, will be performed to complete the data. A fully specified statistical analysis plan will be written before unmasking of the data.

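### Univariate screening and forward Cox selection over 9 to 11 echo indices would declare a chance predictor significant in roughly 20-40% of trials if none is prognostic

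*Protocol article*

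**What the plan says.** The prognostic-factor analysis is described in Statistical analyses. The Cox model, "with the use of forward selection based on the likelihood ratio test, will be implemented for multivariate analysis", takes its candidates from univariate results. Its stated purpose is to find which of the factors that emerged there, "including mitral inflow velocities, DT, IVRT, mitral annular velocities, LA volume, and LA strain were significantly related to clinical events in the follow-up period". The selection method, its source (a univariate screen of the same data) and the form of the conclusion are therefore all fixed.

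Outcome measurements shows how many variables the named groups contain. Mitral inflow is E and A, and the annular velocities are Ea and Aa. Strain has two components: "LA strain (global systolic and diastolic LA strain". It adds that "Mitral E/A and E/Ea ratios will be calculated".

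Neither an entry level for the forward steps nor a threshold for the univariate screen is stated. The only level in the section is the general one, "0.05 will be considered statistically significant", which closes the paragraph on the safety dataset. No multiplicity adjustment, shrinkage, validation, limit on model size or exploratory label is attached to this analysis.

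The Sample size section gives 62 patients and concedes that "this study is likely to be underpowered in terms of assessing secondary outcomes". No event rate or expected event count appears anywhere.

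**The concern.** Forward selection picks the variable with the largest test statistic and then reports the p-value as if that variable had been the only one examined. With about ten candidates, the largest of ten chance statistics passes a 5% threshold far more often than 5% of the time. A univariate screen on the same patients gives no protection, because a variable that passes by chance there passes by chance again at the first forward step.

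At stake is a published statement that a particular echo index predicts clinical events, carrying a p-value without its usual meaning and a hazard ratio that is too far from 1 because only large estimates survive selection. The power remark in Sample size warns the reader about effects that may be missed. It says nothing about effects that may be found by chance.

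**Working it through.** **The plan's own figure.** The article states no figure for the Cox analysis. The 62 comes from the primary E/E' comparison (difference 5.0, SD 5.0, two-sided 5%, power 90%, loss 30%). The normal formula gives n = 2 × (1.960 + 1.282)² × 5.0²/5.0² = 21.01 per arm, so 22. Dividing by 0.70 gives 21.01/0.70 = 30.0 or 22/0.70 = 31.4, which brackets the stated 31 per arm. The figure reproduces to within a patient or two, but it does not size the Cox analysis.

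**Number of candidates, k.** Counted singly: E, A, DT, IVRT, Ea, Aa, LA volume, systolic LA strain and diastolic LA strain make k = 9. Adding E/A and E/Ea makes k = 11. The list is introduced as non-exhaustive, so k could be larger.

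**Entry level.** Assumed 0.05, i.e. a likelihood-ratio statistic above 3.841 on one degree of freedom. A looser level would raise the rates below and a stricter one would lower them. The screen is assumed to be no stricter than the entry level; it then removes nothing that would have entered at the first step.

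**Independent candidates, none prognostic.** P(at least one selected) = 1 − 0.95^k:

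- k = 9: 37%
- k = 10: 40%
- k = 11: 43%

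**Correlated candidates, none prognostic.** The model is non-empty exactly when the largest univariable statistic passes the entry level, so simulating the first forward step is enough. Univariable Cox likelihood-ratio tests were simulated with N = 62, equicorrelated normal predictors, 3 to 19 events and 4000 trials per setting:

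| Correlation | k = 9 | k = 11 |
|---|---|---|
| 0 | 38-40% | 45-48% |
| 0.3 | 33-36% | 38-41% |
| 0.5 | 28-30% | 32-34% |
| 0.7 | 20-23% | 24-25% |

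The ranges within cells run over the event counts and show no material trend. At correlation 0 the simulated rates lie slightly above the formula because the small-sample test itself rejects a little too often, in about 5.2-5.6% of single tests; at 5.5%, 1 − 0.945^9 = 40% and 1 − 0.945^11 = 46%. With N = 44, roughly what remains of 62 after 30% loss, the results are close to the same.

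**Events per candidate.** Assumed 12-month event rates of 5%, 10%, 20% and 30% give about 3, 6, 12 and 19 events, or 0.3 to 2.1 per candidate. Even if all 62 patients had an event, the ratio would be only 62/11 = 5.6 to 62/9 = 6.9.

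**Size of the hazard-ratio bias.** In a simulation of the same kind (10 noise predictors, N = 62, true hazard ratio 1.0), the falsely selected variable had a median hazard ratio per SD, inverted if below 1, of about 2.9, 2.3 and 1.9 at assumed event rates of 10%, 15% and 25%. Unlike the false-selection rate, this bias does depend on the event count, and it is worst when events are few.

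**The case against.** **The percentages assume that no index is prognostic.** Correct. A reader might infer that the markers this trial publishes would be mostly noise. The calculation cannot show that, because it sets every candidate to noise, and the documents do not say that none is related to outcome. What stands is conditional: if none is, a false marker is reported often.

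**The independent case is unrealistic.** Also fair. Velocities, their ratios and the two strain components are likely to be correlated, so the 37-43% figure should not be quoted alone. The correlated rates remain several times 5%.

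**A family-wise rate is set against a per-test level.** The protocol does not promise family-wise control here. But the stated aim is to name which of several indices are significant, so the chance that at least one is named falsely is the relevant quantity.

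**The entry level and the number of events are not stated.** The 0.05 level is an inference. It is also tempting to say that there will be only a handful of events. Stable patients in NYHA class I to III make that plausible, but Trial objectives counts symptom severity as well as heart failure hospitalization among clinical events, so the number could be larger. The false-selection rate does not rest on it.

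**The promised analysis plan may settle this.** It may settle details. Whether treatment is forced into the model, and which visit's echo values are used, are matters that an article can leave to that plan, and their absence is no fault here. The selection procedure and the significance claim are different: the article has already chosen them.

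**The analysis is ancillary.** True. Finding prognostic markers is not among the listed objectives, which limits the importance of the point.

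**Conclusion.** The point holds as a fault in a stated analysis choice. If the plan is followed as written, and no echo index is prognostic, at least one is declared significantly related to events in roughly 20-40% of trials, with the upper end slightly exceeded if 11 candidates are independent. This rests on two assumptions: entry at 0.05, and a screen no stricter than that. It does not rest on the event count. Whatever the truth about the indices, p-values and confidence intervals computed after selection are not valid, and the hazard ratios of selected indices are overstated. The primary E/E' comparison and the log-rank comparison of the arms are untouched, so this is a moderate matter that should be corrected but does not threaten the trial's main result.

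**What to change.** Replace the univariate screen and forward selection with one small Cox model whose covariates are named in the analysis plan before the data are unmasked. Use baseline echo values only, so that every predictor is measured before the events it is meant to predict. Limit the number of covariates by the event count, and use a penalised fit such as Firth's if events are few. Report hazard ratios with confidence intervals, label the analysis exploratory and make no significance claims. Which echo covariates to keep is for the investigators to decide in advance; the documents give no ground for prescribing a single one.

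The change needs no new data, only revised text in the protocol and the coming analysis plan. Its cost is scientific: fewer echo markers are examined jointly as predictors.

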## Discussion

Aging represents both a convergence of declining cardioprotective systems and increasing disease processes that are fertile ground for the development of HF [2]. With 50 % of all HF diagnoses and 90 % of all HF deaths occurring in the segment of the population over age 70, HF is largely a disease of older people. In addition, the greatest proportion of older HF patients have preserved systolic function [1].

Patients with HF can be divided into two different groups based on EF: HF with preserved or reduced EF [13]. The two are similar in terms of prevalence and mortality rate [14, 15]. However, current HF guidelines do not address the use of β-Blockers in patients with preserved EF [16] because no effective treatment has been identified in randomized clinical trials.

β-Blockers are thought to potentially improve diastolic filling by a negative chronotropic effect [17]. Some studies support the use of β-Blockers in patients with preserved EF [18, 19]. Notably, recent data suggest that the effect of the β-Blocker nebivolol is similar in HF patients with preserved and impaired EF [9]. Increased nitric oxide release induced by nebivolol [20] may encourage early LV relaxation [21].

Randomized clinical trials and meta-analyses have shown that long-term use of β-Blockers improves LV systolic function and clinical outcomes of HF patients with reduced EF. The average age of subjects in these placebo-controlled mortality and morbidity studies of β-Blockers in HF has been below 70 years [3–5]. Several β-Blockers are available, but only four, carvedilol, metoprolol, bisoprolol, and nebivolol, have been successfully tested in HF and are used in treatment of the condition [22, 23]. However, comparison studies on the efficiency of different β-Blockers in the treatment of HF are limited [23, 24]. At present, little data are available on the comparative effectiveness of carvedilol and nebivolol for HF. A recent study found that carvedilol and nebivolol appear to similarly improve LV diastolic functions in nonischemic HF patients [25]. However, that study did not involve an HF population with preserved EF. Thus, the current trial will be the first head-to-head comparison of the diastolic effects of nebivolol and carvedilol in HF patients with preserved EF.

With regard to possible risks of bias, we anticipate that the risk of selection bias is low, due to the use of adequate methods for sequence generation and allocation sequence concealment. Regarding performance, participants might be influenced by knowledge of group assignment; however, the possibility that unblinding to group assignment may result in an overestimation or an underestimation of intervention effects is low. In addition, as reported above, the risk of attrition bias due to missing data has been adequately prevented and will be treated.

## Trial status

Recruitment is ongoing at the time of manuscript submission.

## Abbreviations

ACE: Angiotensin-converting enzyme
EF: Ejection fraction
HF: Heart failure
LV: Left ventricle
NYHA: New York Heart Association
SENIOR: Study of the Effects of Nebivolol Intervention on Outcomes and Rehospitalization in Seniors with Heart Failure
